### Research hypotheses

We expect the FutureU for Mental Health intervention to be broadly accepted and feasible to implement. We expect participants to feel embodied and engaged with the virtual environment and intervention exercises.

We hypothesize that the FutureU for Mental Health (FutureU-MH) virtual reality intervention (Coping Plan plus Self-Help and Positive Future Memories interventions, collectively) will reduce negative affect, depressive symptoms, and severity/frequency of suicidal ideation, and improve mood by enhancing the quality of mental imagery in thoughts of the future and of the future self. We hypothesize this effect will continue to grow over time as participants practice a new way of thinking and cognitive patterns gradually change. Specifically, participants who receive the Coping Plan intervention plus FutureU-MH (TX: the treatment group) are expected to see an improvement in the quality of mental imagery in thoughts of the future (vividness) and of the future self (vividness, valence, connectedness, and similarity), while no change in quality of thoughts is expected for participants who receive only treatment as usual, the coping plan intervention (TAU: the control group). In turn, we expect that participants receiving TX will subsequently show a greater reduction in negative affect, depressive symptoms, and severity/frequency of suicidal ideation and a greater improvement in mood than participants receiving TAU. Similarly, participants receiving TX are expected to see an improvement in the quality of mental imagery in thoughts of the future and of the future self, while no change in quality of thoughts is expected for participants receiving TAU. These effects will be strongest at the 1-week and 3-month follow-ups.

Finally, in a more highly powered study, we hypothesize that this intervention would be most effective for individuals experiencing executive dysfunction as the images and structure provided by the virtual environment (VE) and intervention exercise will reduce the cognitive demands required to generate vivid future-oriented thought. Although we are not powered to assess this hypothesis in this pilot trial, we include the assessment measures to understand whether administration of these lengthier measures is feasible.

## Methods/design

### Study design and timeline

The intervention is designed as a randomized, controlled, participant-blind, add-on superiority trial with three parallel groups. Block randomization will occur with a 1:1 allocation. All participants will receive a Coping Plan intervention [24]. Participants only randomized to receive the Coping Plan will constitute the TAU control group. The TAU control design was chosen to ensure ethical responsiveness to the needs of all participants. Participants in each of the two treatment arms will additionally receive the FutureU-MH intervention. As the intervention is administered via two sessions each targeting different elements of the future self, treatment groups will follow an AB/BA design to allow for differentiation of session effects.

Participants will be assessed at 5 time points: pre-intervention (prior to randomization and completion of the Coping Plan), post-Coping Plan, pre- and post- each intervention session, and at both 1-week and 3 months follow-up (see SPIRIT figure in Table 1). These methods were in accordance with the Declaration of Helsinki and approved by the Ethics Council of the Max-Planck Gesellschaft.

**Table 1 Tab1:** SPIRIT Figure for FutureU for Mental Health Trial

	Timepoint	− 1	0	t1	t2	**t3**	**f1**	**f2**	
Activity/assessment	Approx. time to complete	Screening and online consent	Baseline assessment	TAU: coping plan	Intervention P1 and pre-post assessments/or interim assessment 1 (Control)	Intervention P2 and pre-post assessments/or interim assessment 2 (Control)	1 week follow-up	3 month follow-up	End of study
Enrollment:									
Pre-screening consent	1 min	X							
Screening	3 min	X							
Informed consent (online)	10 min	X							
Random allocation	N/A		X						
Interventions:									
Coping plan intervention (TAU)	25 min			X					
Self-help intervention (in VR)	30 min				E *or*	E *or*			
Positive future memories intervention (in VR)	30 min				E	E			
Assessments:									
Demographics	5 min		X						
Beck Depression Inventory—II	10 min		X					X	
C-SSRS	5 min		X		X	X	X	X	
Self-efficacy	3 min		X					X	
Self-reported future self and mood	10 min		X		X	X	X	X	
Prospective imagery task	5 min		X					X	
BRIEF-A	15 min		X						
Engagement/embodiment	3 min				E	E			
Feasibility outcomes	N/A								X
Acceptability, feasibility, appropriateness	3 min				E	E			
Intervention use	1 min					E	E	E	

*TAU *treatment as usual, *VR *virtual reality,* X *all participants complete, *E *experimental groups complete, *C *control group completes

Analysis will take place at George Mason University. On the recommendation of the George Mason University Institutional Review Board, approval for analysis of the dataset will be obtained prior.

A reference guide for information outlined in the SPIRIT 2013 Checklist can be found in the supplemental materials.

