### Recruitment, screening and randomization

#### Recruitment, screening and randomization

All participants will be recruited from the community in Freiburg im Breisgau, Germany. Recruitment will be done via fliers placed around the city of Freiburg (i.e., on flier boards, on bicycles, etc.) and through the Max-Planck Institute’s MAXLab SONA system, which currently contains ~ 250 active participants. Fliers will be replenished around the city weekly and will include a QR code that will direct potential participants to the SONA system registration page. There, they will be directed to create an account and to take a screener questionnaire, consisting of the PHQ-9 and the BDI-II suicide item. If eligible for the study, they will immediately be directed to the online study consent form, from which they will be given a password to sign up for the first in-lab session on Qualtrics.

During the first in-lab session, participants will review the consent with the experimenter and then answer the baseline assessment battery. Following the completion of the baseline assessment, participants will be randomized to either the control condition or one of the treatment conditions. Randomization will follow a 1:1 allocation.

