#### Virtual therapist

The virtual therapist avatar will be controlled by the experimenter and was designed in her likeness to enhance the sense of realness for participants once in the VR – see Fig. 4. The experimenter will be the same for all participants.

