### Interventions

Three interventions will be administered. First, as a treatment as usual control (TAU), a Coping Plan is administered by the experimenter during the first in-person session to all participants. Next, participants in the treatment condition (TX) will all receive the Self-Help Intervention (SH) and the Positive Future Memories Intervention (PFM)—collectively known as the FutureU for Mental Health (FU-MH) Intervention. Participants in the TX condition will be assigned to either group A or B, which will dictate the order in which the SH and PFM interventions are received. Group A will first receive SH and then PFM; Group B will first receive PFM and then SH.

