### Outcomes measures

All measures taken during in-lab sessions will be conducted on a laptop in the lab space. All measures taken during follow-up and online control sessions will be self-administered by participants via link to a Qualtrics survey.

*Primary objective measures—feasibility and acceptability of the intervention*
Feasibility: Number of eligible participants, willingness of participants to fully participate
(i)Rates of recruitment into the studyNumber of potentially eligible participants on SONA systems.Number of participants who completed the PHQ-9 screener and BDI-II item.Number (and proportion) of participants who were eligible to participate.Number (and proportion) of participants who were ineligible to participate at screening and why.Number (and proportion) of participants who consented to participate in intervention.Number (and proportion) of participants who scheduled the first in-lab session.Number (and proportion) of participants who completed the first in-lab session.(ii)Retention to treatmentNumber (and proportion) of participants who successfully completed all parts of the intervention (sessions 1, 2, and 3).Number (and proportion) of participants who drop out of the study and, when freely shared, reasons for drop out. In accordance with our informed consent, participants are free to drop out of the study at any point without explanation.(iii)Completion of between session tasks(iv)Number (and proportion) of participants who report needing to use their Coping Plan.(v)Number (and proportion) of participants who report using their Coping Plan when needed.(vi)Number (and proportion) of participants who report listening to their Self-Help recording in the week following the intervention session and 3 months following the intervention session.(vii)Number (and proportion) of participants who report listening to their Positive Future Memories recording in the week following the intervention session and 3 months following the intervention session.(viii)Attrition at post-treatment follow-up pointsNumber (and proportion) of participants who complete the 1-week follow-up questionnaire.Number (and proportion) of participants who complete the 1-month follow-up questionnaire.(ix)Levels of missing clinical outcome dataProportion of data completion for each questionnaire at each time-point.

Feasibility: Adherence/Compliance rates—Rating and adherence to intervention protocol. See above for details.

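### The participant-blind label does not fit a VR versus no-VR comparison, and allocation precedes the shared Coping Plan with no masking of the experimenter described

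*Protocol article*

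**What the plan says.** The label appears in the Methods paragraph of the Abstract and again under Study design and timeline: "The intervention is designed as a randomized, controlled, participant-blind, add-on superiority trial with three parallel groups." No other role is described as blinded.

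The same section defines the arms. For controls: "Participants only randomized to receive the Coping Plan will constitute the TAU control group." For the others: "Participants in each of the two treatment arms will additionally receive the FutureU-MH intervention." In Table 1 both VR rows are marked for the experimental groups only.

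On the setting of assessments, Outcomes measures says: "All measures taken during follow-up and online control sessions will be self-administered by participants via link to a Qualtrics survey."

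On sequence, Recruitment, screening and randomization says: "Following the completion of the baseline assessment, participants will be randomized to either the control condition or one of the treatment conditions." Table 1 agrees, with random allocation at timepoint 0 and the Coping Plan at t1. The Interventions section says that "a Coping Plan is administered by the experimenter during the first in-person session to all participants", and Virtual therapist adds: "The experimenter will be the same for all participants." That person also controls the therapist avatar in the VR sessions.

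Under Analyses, the secondary-objective section compares treatment with control by independent-sample t-tests and latent growth curves. Its caveat on interpretation concerns the statistical limits of a pilot and does not mention blinding.

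**The concern.** A blinding label tells the reader which biases have been dealt with. If participants did not know their condition, differences in self-reported mood or imagery could not easily be put down to hope, disappointment or a wish to please the therapist. Here one arm wears a headset, meets an age-progressed avatar and spends two further sessions with a therapist, while the other fills in online questionnaires. The outcomes compared are future-self scales, prospective imagery, BDI-II, PANAS, self-efficacy and a self-report C-SSRS whose answers the experimenter confirms (Safety protocol). These are the kinds of outcome that respond to expectation.

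The second part concerns the add-on structure. The Coping Plan is the common background in all arms and the control arm's only treatment, and it supplies material for the VR exercises. An add-on contrast isolates the VR only if that background is delivered alike in every arm. With allocation placed before it, and one person delivering both components, nothing described in the article protects that likeness.

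The trial is meant to inform a full-scale RCT. A contrast inflated by expectancy, reported under a blinding label, could carry over into that trial's assumptions.

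**Working it through.** The article gives no figure for blinding or bias, so there is none to reproduce. The check is mainly a comparison of what each arm experiences.

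| Feature | Treatment (A and B) | Control | Where stated |
|---|---|---|---|
| Coping Plan | yes | yes | Interventions; Table 1 |
| VR sessions | two, 30 minutes each | none | Table 1 |
| Sham or attention control | not applicable | none described | Study design; Interventions |
| Assessments at t2 and t3 | before and after each VR session | interim assessments in online sessions | Table 1; Outcomes measures |

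**Step 1: what could be masked.** Receipt of VR is self-evident to the recipient, and so is not receiving it. Three things could still be hidden: the A/B order, the hypotheses, and the existence of other arms. The article claims none of them. Masking of order would not protect the comparison of both treatment arms with control.

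**Step 2: which results are exposed.** The key secondary objective includes improvement compared with the control group, on self-report measures. The primary objective is analysed descriptively, and the engagement, embodiment and acceptability scales are completed by the experimental groups only. The exposure is therefore in the secondary between-arm contrasts.

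**Step 3: sequence in session 1.** Baseline, then allocation, then Coping Plan. The person delivering the plan must know the arm by the time VR starts. The article does not say whether that person knows it during the Coping Plan.

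**Step 4: scale, for illustration only.** Inputs are 60 participants with 40 receiving the intervention (Sample size), hence 20 controls, and outcomes in SD units without covariate adjustment.

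- Standard error = √(1/40 + 1/20) = √0.075 = 0.274 SD.
- 95% half-width = t(0.975, 58) × 0.274 = 2.002 × 0.274 = 0.548 SD.
- Assumed bias b of 0.2 to 0.3 SD: 0.2/0.548 = 36% and 0.3/0.548 = 55% of the half-width.
- Chance of a two-sided 5% result with no true effect (normal approximation) = Φ(b/0.274 − 1.96) + Φ(−b/0.274 − 1.96).

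| Assumed bias (SD) | Chance of a significant difference |
|---|---|
| 0 | 5.0% |
| 0.1 | 6.5% |
| 0.2 | 11.3% |
| 0.3 | 19.5% |
| 0.5 | 44.7% |

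Every bias size in the table is an assumption, not a figure from the document.

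**The case against.** The strongest reply is that this is a pilot. Its main question is feasibility and acceptability, progression rests on those outcomes, the secondary analyses are offered as exploring trends, and the article says it is not powered for clinical effects. That stands, and it limits the point to the secondary contrasts. It does not make the label correct.

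It can also be said that participants may have been kept unaware of the hypotheses or of the other arms, and that a condensed article leaves such detail to the full protocol or consent form. This too is fair, and it is why calling the trial wholly open-label is not established. But no fuller document could make VR and no VR indistinguishable to the person concerned.

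A reader might infer three stronger things that the text does not support:

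- *That the plan claims bias is excluded.* It nowhere says so; the label only implies protection.
- *That the experimenter is known to be unblinded at every Coping Plan.* The order of steps allows this, but when the experimenter learns the arm is not stated.
- *That any bias must favour VR.* Expectancy in participants would be expected to do so. An experimenter aware of allocation could instead put more effort into the control arm's only treatment.

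Finally, allocating straight after baseline is ordinary practice, and the article does not contradict itself on that order. The resequencing proposed below is a safeguard, not the correction of an error.

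**Conclusion.** The point holds in limited form. As written, the participant-blind label describes a property that the design does not have for the treatment-versus-control comparison. This rests on the article alone, with no numerical assumption. The between-arm self-report results should be read as unblinded and open to expectancy and demand effects.

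The sequencing part is weaker. Allocation does precede the shared Coping Plan, and the same person delivers both components, so influence on its delivery is possible but not shown.

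The size of any bias cannot be derived from the document. If it were 0.2–0.3 SD, it would raise the chance of a spurious significant t-test on a given outcome from 5% to about 11–20%. That is enough to matter for proof-of-concept claims. It gives no ground for saying that the feasibility or acceptability conclusions, or the progression decision, are undermined.

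**What to change.** 1. In the Abstract and under Study design and timeline, delete participant-blind, or replace it with a statement of exactly what participants are unaware of (session order, and the hypotheses or other arms only if these are in fact withheld).
2. In the secondary-objective part of Analyses, add that between-arm differences on self-report measures are unblinded with respect to VR receipt and open to expectancy bias, alongside the existing caveat on pilot size.
3. If the stage of the trial still allows, make or reveal the allocation only after the Coping Plan within session 1, and amend Recruitment, screening and randomization and Table 1 to match. Photographs for avatars are already planned in session 1 for each participant, so they do not require earlier allocation. If the order can no longer change, state when the experimenter learned the allocation.
4. Reconcile the post-Coping-Plan assessment listed under Study design and timeline with Table 1, which shows no assessment at t1. If it is collected, it should also come before allocation is revealed.

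The cost is a less favourable blinding label, a few sentences and a small change in step order. If the post-Coping-Plan assessment is not already part of the session, adding it would also take some participant time.

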#### Coping plan intervention

The Coping Plan is an adaptation of Stanley and Brown’s [23] safety plan and is intended for use with people who struggle with regulating negative emotions but who do not report suicidal ideation [24]. The structure of the plan is the same as the Safety Plan but excludes the section on ‘Keeping the Environment Safe’. For participants who report suicidal ideation, the Safety Plan format (i.e., including ‘Keeping the Environment Safe’) will be used. The Coping Plan exercise will be informed by participants’ responses to the pre-questionnaire (specifically, the BDI-II and C-SSRS which measure depressive symptoms and suicidal ideation) and a follow-up conversation with the therapist about those responses. Participants will identify (a) Triggers and warning signs, (b) Things they can do to help themselves, (c) People or places that can distract them, (d) People they can talk to for help, (e) Professionals they can talk to for help, and (f) Things that make life worth living. A template for the coping plan can be found in Appendix 1.

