#### Secondary objective—establishing a proof of concept for the intervention

Assessment of change in targeted cognitive mechanisms and clinical outcomes will be completed as is outlined in the outcomes section. Due to the modest sample size, these analyses will be completed to pilot the method for a full-scale RCT and to explore trends. The significance of effects will be interpreted and discussed within the context of the statistical limitations of a pilot trial.

Between-group differences for participants in the treatment condition versus the control condition will be assessed using independent-sample *t*-tests. Here, interpretation of Cohen’s *d *will be done using between-group standard deviations. The significance of between-subject changes will also be assessed through calculation of a reliable change index (RCI) [53] and evaluation of confidence intervals for mean differences.

Between-group differences in the targeted cognitive mechanisms and clinical outcomes will additionally be assessed through Latent Growth Curve Modeling (LGCM). This analysis will allow us to evaluate the difference in trajectories of change in cognitive mechanisms and clinical outcomes between the control and treatment conditions. The hypothesized changes in thought processes and subsequent clinical outcomes are expected to continue to grow over time post-intervention, rather than improve wholly and discretely at the point of intervention. The LGCM approach will allow us to observe whether this growth hypothesis is borne out.

For all analyses, age and gender will be included as covariates. Gender is included for the potential biasing effect on reports of depression. Cross-nationally, women endorse depression at highly elevated rates versus men [54]. Age is included for the potential biasing effects on future-oriented thinking. The future is conceived differently at different stages of life. Although variation in stages of life is comparatively low given the already constricted age range (18–24), there are still some meaningful differences in life stage that may impact future perspective when comparing an 18 versus 24-year-old.

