### Progression criteria

Decisions regarding whether and how to proceed with testing this intervention on a larger scale are based on the feasibility and acceptability outcomes outlined above. Progression criteria are described in Table 2, following best-practice recommendations for progression criteria reporting [55].

**Table 2 Tab2:** Progression criteria

	Go: proceed with RCT	Amend: proceed with changes	Stop: do not proceed unless changes are possible
Feasibility of participant recruitment Can 60 participants be recruited who meet eligibility criteria (20 per group)?	If ≥ 12 participants can be recruited per month, 60 total	If ≥ 8 participants can be recruited per month, 40 total	If no participants can be recruited per month
Feasibility of participant retention Can ≥ 85% of participants be retained in the study until completion?	≥ 85% (95% CI*: 74–92%) retained through session 4 (1 week follow-up)	≥ 60% retained through session 4 (1 week follow-up)	< 60% retained through session 4 (1 week follow-up)
Intervention implementation Based on qualitative and quantitative data from both participants and experimenter	Delivery of intervention judged strongly feasible	Delivery of intervention judged feasible	Delivery of intervention judged possibly feasible
Feasibility of between-session tasks	≥ 60% participants complete between-session tasks	≥ 40% participants complete between-session tasks	< 40% participants complete between-session tasks
Feasibility of virtual reality medium (embodiment and engagement)	≥ 85% participants report acceptable ratings for avatar embodiment, engagement, and recognition	≥ 60% participants report acceptable ratings for avatar embodiment, engagement, and recognition	< 60% participants report acceptable ratings for avatar embodiment, engagement, and recognition
Acceptability of intervention Based on qualitative and quantitative data from both participants and experimenter	Intervention judged highly acceptable	Intervention judged acceptable	Intervention judged potentially acceptable

*Wilson interval calculated based on a sample of *n *= 60

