### Safety protocol

Participants are asked to answer questions regarding suicidal ideation, as such a safety protocol was developed to ensure that any participant who presents as at risk for suicide receives adequate care. As a part of the study procedure, participants will respond to a self-report version of the C-SSRS for research. Immediately following completion of the questionnaires, the experimenter—who is a trained therapist—will review participant responses and confirm answers to the C-SSRS, using the full baseline/screening version of the measure. If a participant reports suicidal ideation, the experimenter will review the additional suicidal ideation intensity questions and suicidal and nonsuicidal self-injury behavior items with the participant. Following a review of participant answers, the experimenter will then complete a Safety Planning intervention with the participant in lieu of the Coping Plan intervention. The Safety Planning intervention is currently the best practice for responding to suicidal ideation. Participants will be given a copy of the plan to take home and (all participants) will be provided with a resource sheet of local and national mental health resources. Participants will be encouraged to consult their plan and the resource sheet. In the case of suicidal ideation, participants will be offered consultation with a licensed clinical psychologist, who is consulting on the study. In the case of significant risk (as deemed by the experimenter), the licensed clinical psychologist will be contacted for consultation on how to proceed. All risk procedures will be documented in the participant’s study file. The experimenters will not be made aware of whether participants chose to pursue subsequent mental health services. In the unlikely case of an acute mental health crisis in the lab, participants are informed through the consent that the experimenter may call emergency services to ensure they receive the best care possible.

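### Baseline suicidal ideation is known before allocation and decides which plan is given, but it is neither a stated covariate nor a named randomisation stratum

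*Protocol article*

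**What the plan says.** Under Study design and timeline, the protocol article states "Block randomization will occur with a 1:1 allocation". Under Recruitment, screening and randomization it repeats "Randomization will follow a 1:1 allocation". Neither place names a stratification factor.

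Ideation is known before allocation. The online screener is described as "consisting of the PHQ-9 and the BDI-II suicide item". Table 1 puts the BDI-II and the C-SSRS in the baseline column, and the text says "Following the completion of the baseline assessment, participants will be randomized to either the control condition or one of the treatment conditions".

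Ideation also decides which version of the shared plan is delivered. The section on the Coping Plan says "For participants who report suicidal ideation, the Safety Plan format" is used. The Safety protocol says that, where ideation is reported, the experimenter will "complete a Safety Planning intervention with the participant in lieu of the Coping Plan intervention". The rule is the same in every arm.

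Outcomes measures lists a larger reduction in ideation in the treatment condition than in the control condition as a secondary outcome. The analysis section for the secondary objective then fixes the adjustment set: "For all analyses, age and gender will be included as covariates". Each of the two covariates is given a reason. Baseline ideation is not mentioned.

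**The concern.** Ideation is a strong candidate for balance or adjustment for three reasons: it is measured in time, it determines what participants in all arms receive at the first session (for controls, the whole intervention), and it is the baseline of an outcome that appears in the article's title. Entry does not require it: a PHQ-9 score above 4 is enough, and only the top category of the BDI suicide item is excluded. The number of participants with ideation is therefore left to chance, and so is their split between 20 controls and 40 treated.

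If the split is uneven, the arms differ at the start in severity and in the mix of plan versions. The stated covariates do nothing about either. The ideation, depression and affect contrasts would each carry that difference.

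**Working it through.** **Inputs.** Arm sizes come from Table 2 (60 in total, 20 per group) and the sample size section (40 receiving the intervention). They agree: 3 × 20 = 60 and 2 × 20 = 40. The stated 1:1 ratio is therefore read as 1:1:1 over three groups, since a two-way 1:1 split would give 30 and 30. The article gives no prevalence of ideation, so it is assumed: K = 9, 12, 15, 18 or 24 of 60 (15%, 20%, 25%, 30%, 40%).

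**Distribution.** Without stratification, the number x of controls with ideation is hypergeometric (60 participants, K with ideation, 20 drawn). Simulating unstratified permuted blocks of 3 and of 6 gave the same result.

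**Arm difference.** The difference in proportions is x/20 − (K − x)/40 = (3x − K)/40 = 0.075 × (x − K/3). Each participant away from the expected K/3 moves it by 7.5 points. For these values of K, a gap of 15 points or more means being off by at least two people, and 20 points or more means at least three.

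| K (assumed) | Expected controls with ideation | P(gap ≥ 15 points) | P(gap ≥ 20 points) | P(two or fewer controls) |
|---|---|---|---|---|
| 9 (15%) | 3 | 0.25 | 0.05 | 0.36 |
| 12 (20%) | 4 | 0.30 | 0.08 | 0.15 |
| 15 (25%) | 5 | 0.34 | 0.11 | 0.05 |
| 18 (30%) | 6 | 0.37 | 0.13 | 0.015 |
| 24 (40%) | 8 | 0.40 | 0.16 | 0.0006 |

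**What a gap does to a contrast.** If participants with and without ideation differ by δ on an outcome, a gap g shifts the unadjusted contrast by g × δ. With g = 0.15 and δ of one standard deviation (assumed), the shift is 0.15 SD. The standard error of a 20 versus 40 comparison is √(1/20 + 1/40) = 0.27 SD, so the shift is about half a standard error. With δ = 0.5 SD the shift is 0.075 SD.

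**What stratifying does.** Blocks of 3 within ideation strata fix the control count at K/3 for these K. Blocks of 6 gave at most one more or one fewer in the cases simulated. The expected count does not change. Among participants with ideation, the standard error is proportional to √(1/x + 1/(K − x)). Averaged over draws in which it can be computed and divided by its value at x = K/3, it is 1.07, 1.06, 1.04 and 1.02 for K = 9, 12, 15 and 24. On average, then, leaving out the stratum inflates that standard error by only 2% to 7%.

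**The case against.** The strongest reply is that the missing stratum is silence. A journal article commonly leaves block sizes and strata to the full protocol, which is not shown, and nothing here denies stratification. That stands, and it makes the stratification advice conditional. It does not reach the covariates, because the article states them explicitly for all analyses.

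A second reply is that the between-arm analyses are exploratory. The article says that they pilot the method and explore trends and that the trial is not powered for clinical outcomes. No clinical result enters the progression criteria. This also stands and limits the weight of the point.

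A third reply is that baseline is not ignored, because outcomes are framed as change from baseline and growth models are planned. This is partly right for the ideation outcome. It does not help depression or affect, where ideation and plan version are separate baseline differences.

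A reader might go further and infer that unstratified randomisation is what would leave too few controls with ideation, making the comparison uninformative. The documents do not support that. The count is set mainly by prevalence and the 20-person arm. At 15% prevalence stratifying delivers three such controls, and at 40% the chance of two or fewer is already 0.0006. The comparison is also planned in everyone, not only in those with ideation.

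A reader might equally infer that giving two plan versions biases the trial. It does not, since the rule is the same in every arm and only chance imbalance can result.

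**Conclusion.** The point holds as one about chance imbalance and adjustment. A variable that is available before allocation, determines the plan version and is the baseline of a named outcome has been left out of an explicit covariate list, and the article names no stratum. Under assumed prevalences of 15% to 40%, the chance of an arm gap of at least 15 points is 25% to 40%, and of at least 20 points 5% to 16%. These figures rest on the assumed prevalence, on 60 participants split 20 to 40, and on there being no stratum in the unseen full protocol. There is no systematic bias, and the feasibility and acceptability objective is unaffected. Adjustment is worth making because it costs almost nothing and because these analyses are meant to rehearse those of the full trial.

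**What to change.** Add baseline ideation beside age and gender in the between-arm clinical analyses. Use any versus none on the self-report C-SSRS completed before allocation or, for the ideation outcome itself, the baseline score. A t-test takes no covariates, so this goes into the same regression form that the age and gender adjustment already needs. Report baseline ideation and plan version by arm. The cost is one extra covariate.

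If allocation has not begun and the full protocol does not already stratify, also keep separate concealed 1:1:1 block lists for participants with and without ideation, with mixed block sizes such as 3 and 6. Base the stratum on the self-report C-SSRS, because the article does not say whether the experimenter's confirmatory review comes before or after allocation. The costs are a second list, arm sizes slightly off 20 when last blocks are unfinished (18 to 22 controls with blocks of 6 in the cases computed), and somewhat more predictable blocks, which the mixed sizes reduce.
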